### Statistical Analysis

#### Primary Endpoint

The primary endpoint for the study is absence of pain or pain reduction reported by the participants at week 12 post-intervention.

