#### Sample Size and Power Calculations

We will enroll a total of 120 participants: 60 participants in The-Optimal-Lymph-Flow intervention and 60 participants in the Arm Precaution control group to account for a potential attrition of 20%, which has been observed in the prior studies in breast cancer survivors [10]. This will yield an adequate analytic sample size. Even with 20% attrition based on a 2 sample 2-sided *t* test with alpha=.05 and power of 90%, we can detect a difference of 0.7 standard deviations in the difference between the presence of pain in the intervention group compared to the control group at 8 weeks or at 12 weeks. The projected sample size will also provide sufficient statistical power for mixed regression models. For linear mixed models of continuous outcomes (eg, pain ratings), statistical power will exceed 80% to detect a medium effect, assuming a constant group effect, correlations of r=.5 between observations, alpha=.05, and compound symmetry of the covariance structure.

For binary outcomes, based on the three repeated observations with a conservative estimate for the assumed correlation of r=0.5 between observations, alpha=.05, sample size of n=50 per treatment arm will have power of 80% to detect odds ratios of the difference between groups ranging from 2.6 to 3.5 (small to medium effects).

Adequacy of sample size will be monitored during the analyses in three ways: (1) assessing sufficiency to estimate the number of model parameters identified by preliminary analyses; (2) examining model fit indices (eg, intra-class correlation coefficient to assess fit of random effects) to ensure data adequately support models generated, and (3) assessing the adequacy to accurately estimate model parameters by generating confidence intervals.

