#### Analysis Plan

We will summarize graphically and numerically the distributions of pain, aching, soreness, tenderness, other symptoms related to lymph fluid accumulation, limb volume differences, BMI, and quality of life as well as covariates (such as medication for pain, age, or education and treatment variable and limb volume and self-care behaviors). The proportion of individuals experiencing pain, aching, soreness, tenderness will be compared between the intervention and control group over time, as will the mean severity ratings and associated quality of life scores. Mean comparisons of number of reported symptoms, limb volume, and BMI will be conducted between the intervention and control group as well as over time.

Bivariate relationships between the variables and treatment group will be assessed using point-biserial correlations and phi coefficients to identify potential covariates for inclusion into statistical models. Linear mixed effects models will be used to analyze continuous outcomes (eg, ratings pain, aching, soreness, tenderness, symptom ratings, and quality of life) and generalized linear mixed models will be used to analyze binary outcomes (presence of pain, aching, soreness, tenderness, and total scores of quality of life). These models will incorporate fixed effects for time, group, and any identified covariates. As indicated by preliminary models to estimate variance effects, models will include random effects for subject-specific slopes and intercepts. A statistically significant fixed effect for group by time interaction will indicate a treatment effect, with the direction of difference determined from mean values. Models will be compared for goodness of fit and modifications to link functions, distributional form, and correlation structure will be made as necessary.

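### The rule for declaring a treatment effect (group-by-time interaction) is neither the test behind the mixed-model power statement nor a test of the week-12 endpoint

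*Protocol article*

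**What the plan says.** Three sections of the protocol article bear on this point.

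- Under **Primary Endpoint**, the article fixes both the outcome and the visit: "The primary endpoint for the study is absence of pain or pain reduction reported by the participants at week 12 post-intervention".
- The section **Sample Size and Power Calculations** plans 60 per arm, which allows for 20% attrition. Its leading calculation is a two-sided two-sample t test at a single visit, week 8 or week 12; with 90% power, "we can detect a difference of 0.7 standard deviations" between the arms. A second statement covers linear mixed models: "statistical power will exceed 80% to detect a medium effect, assuming a constant group effect, correlations of r=.5 between observations, alpha=.05", with compound symmetry. A third covers binary outcomes, with three repeated observations and 50 per arm.
- The **Analysis Plan** uses linear and generalized linear mixed models with fixed effects for time and group, and random intercepts and slopes if indicated. The only stated criterion for efficacy is: "A statistically significant fixed effect for group by time interaction will indicate a treatment effect". Direction is then read from the means. How time is coded, and whether baseline is one of the modelled outcomes, is not stated. The section also mentions comparing proportions and mean severity between groups over time, without naming a test.

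**The concern.** The three sections point to three different quantities: a difference at week 12, a difference averaged over visits, and a change in the difference across visits. A group effect that is the same at every modelled visit has an interaction of exactly zero, so the mixed-model power figure cannot be carried over to the interaction rule.

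Two errors become possible. An intervention with a real week-12 benefit can fail the rule because the interaction test has less power than stated. Conversely, the rule can be met by differences at week 4 or week 8 that have gone by week 12, since direction is taken from means without naming a visit.

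**Working it through.** **Inputs from Sample Size and Power Calculations.** 60 per arm less 20% attrition gives n = 60 × 0.8 = 48 per arm; r = .5; compound symmetry; alpha .05, taken as two-sided. **Assumptions.** Medium effect d = 0.5 SD (the article gives no number; 0.7 SD is shown for range), and complete data among the 48. Below, λ is the noncentrality parameter of a chi-square test. Unless noted, power is from the noncentral chi-square. A simulation of 20,000 runs of the corresponding F tests gave 71% and 64% for the sustained effect, 56% and 72% for the building effect, and 5% for the constant post-baseline case.

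**1. The article's own figures**
- t test, d = 0.7, 48 per arm: 92.4% (90% is reached at 0.67 SD). This agrees with the stated 90%.
- Constant group effect, mean of 3 visits: the variance of a subject's mean is (1 + 2r)/3 = 0.667. λ = d²(n/2)/0.667 = 0.25 × 24/0.667 = 9.0 on 1 df, so power is **85%**. With 4 visits it is 87%. The claim of more than 80% reproduces, as a group main effect.

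**2. The interaction, same inputs**

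For visit as a category, λ = (n/2) × SS(δ)/(1 − r), where δ is the vector of group differences and SS its sum of squares about its mean. For linear time, SS is replaced by the squared projection of δ on the linear contrast.

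| Modelled visits and true differences | Test | λ | Power |
|---|---|---|---|
| Weeks 4, 8, 12: (0.5, 0.5, 0.5) | any interaction | 0 | 5% |
| Baseline + 3: (0, 0.5, 0.5, 0.5) | 3 df | 24 × 0.1875/0.5 = 9.0 | 71% |
| same | linear time | 5.4 | 64% |
| same | 1 df, post mean minus baseline | 9.0 | 85% |
| Baseline + 3: (0, 0.167, 0.333, 0.5) | 3 df | 24 × 0.1389/0.5 = 6.67 | 57% |
| same | linear time | 6.67 | 73% |

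At 0.7 SD with baseline included, the 3-df and linear-time tests have 87% to 96% over the same two patterns.

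**3. Significance without a week-12 difference**

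For δ = (0, 0.5, 0.5, 0), SS = 4 × 0.25² = 0.25 and λ = 24 × 0.25/0.5 = 12.0 on 3 df. The test is significant **84%** of the time although the week-12 difference is zero.

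**4. A week-12 contrast**

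Unadjusted, λ = d²(n/2) = 0.25 × 24 = 6.0; the two-sample t test gives **68%**. Adjusted for baseline with correlation ρ, λ = 6.0/(1 − ρ²):
- ρ = .5: 6.0/0.75 = 8.0, power **81%**.
- ρ = .3: 6.0/0.91 = 6.59, power **73%**.

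**The case against.** The strongest reply is that the trial is not sized on the mixed-model sentence. The leading calculation is a t test at a single visit, and it reproduces. A reader might infer that the whole trial was sized for a constant effect; the article does not support that, because the assumption belongs to one of several power statements. A reader might also infer that week 12 is never tested on its own. That goes too far: the power section refers to a t test at week 8 or week 12, and the Analysis Plan mentions group comparisons over time. What stands is that the Analysis Plan does not carry the t test forward and names no week-12 contrast.

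The size of the power loss also depends on coding that the article leaves open. The 5% case requires baseline to be left out of the outcome vector, whereas the abstract describes a pre- and post-test repeated-measures design. The three observations appear only in the binary paragraph. For that form of the endpoint, however, the case is not far-fetched: patients reporting no pain, aching, tenderness or soreness are excluded, so presence of any of these is universal at baseline in both arms and carries no group contrast. With baseline included and a sustained effect, a 1-df post-versus-baseline contrast loses nothing, and at 0.7 SD power is ample.

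Finally, time coding and contrasts are often left to an SAP, which is not shown. That covers the coding. It does not cover the interaction rule, which the article states outright and which an SAP would have to contradict.

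**Conclusion.** The point holds in a limited form. The criterion for declaring efficacy is not the quantity for which the mixed-model power was computed, and it is not the stated endpoint. On the article's inputs and an assumed 0.5 SD, power is 57% to 73% under the usual codings with baseline included, against the stated figure above 80%. The extremes are 85% for one particular contrast with a sustained effect, and 5% if only post-baseline visits are modelled and the effect is constant. It would therefore be wrong to say flatly that the stated power cannot be reached.

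The mismatch with week 12 does not depend on the effect-size assumption in the same way: an omnibus interaction does not isolate that visit whatever its power, as the 84% example shows. All figures rest on 48 completers per arm, complete data and compound symmetry. The random slopes that the Analysis Plan allows were not modelled.

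**What to change.** 1. Make the primary test the between-group difference at week 12, reported with its 95% CI, from a repeated-measures model of weeks 4, 8 and 12. Include categorical time, group, group-by-time, and the baseline value as a covariate where the outcome varies at baseline.
2. Remove the rule that a significant interaction indicates a treatment effect.
3. Restate the mixed-model power for that contrast, with 0.5 SD named as the assumed effect and 48 per arm: about 81% if the baseline correlation is .5, about 73% if it is .3, and about 68% without baseline adjustment.
4. Give power separately for the binary absence-of-pain form, as a week-12 contrast; the SD-based figures do not cover it.

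The cost is a change of wording in two sections, made before unblinding. No extra patients or data are needed. The downside is a somewhat less favourable stated power.

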#### Interim Analyses

No interim analysis will be conducted since the intervention is only 12-week long.

#### Method of Handling Missing Data and Non-Adherence to Protocol

Data from participants who are missing >20% of any scale will be excluded from calculation of that scale, though remaining data meeting requirements for completeness will be retained. Analysis of missing data will first determine whether it can be assumed to be missing at random (MAR) or not missing at random (NMAR). Based on the results of this step, appropriate methods will be selected for addressing missing data (eg, Heckman Selection for NMAR, Multiple Imputation for data which are MAR).

Further, mixed effects regression models are robust in the presence of missing data. Unlike traditional repeated measures designs (eg, repeated measures ANOVA) which employ listwise deletion, excluding all records for individuals who miss a single observation, mixed effects models are capable of incorporating all completed observations for estimations. Although our previous studies suggest that we will have a limited number of missed observations, individuals need not have the same number of observations. This maximizes the statistical power of our analyses and reduces the likelihood of systematic bias in estimates.

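### The plan lets the collected data decide between MAR and NMAR and selects the missing-data method from the answer, which observed data cannot supply

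*Protocol article*

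**What the plan says.** In the protocol article, the section Method of Handling Missing Data and Non-Adherence to Protocol gives a completeness rule for individual scales and then a two-step rule. The first step is: "Analysis of missing data will first determine whether it can be assumed to be missing at random (MAR) or not missing at random (NMAR". The second is: "Based on the results of this step, appropriate methods will be selected for addressing missing data", with the candidates given as examples: "eg, Heckman Selection for NMAR, Multiple Imputation for data which are MAR".

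The next paragraph of that section says that "mixed effects regression models are robust in the presence of missing data". It contrasts them with listwise deletion in repeated-measures ANOVA and credits them with a lower risk of systematic bias. It attaches no MAR condition, and it does not say how these models relate to the method that the first step selects.

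Two other sections bear on the point. The Analysis Plan assigns linear mixed models to continuous ratings and states that "generalized linear mixed models will be used to analyze binary outcomes", presence of pain among them. Under Primary Endpoint the article says: "The primary endpoint for the study is absence of pain or pain reduction reported by the participants at week 12 post-intervention". Nothing exempts that endpoint from the two-step rule.

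**The concern.** The rule asks the data a question that they cannot answer. Under MAR, missingness is unrelated to the unseen value once the observed values are taken into account. Under NMAR it is still related. The two differ only in something that was not recorded, so the same observed data fit both.

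Two things follow. The handling of the week-12 pain endpoint becomes a choice made after the data are seen, on an uninformative basis. And a look at dropout patterns that happens to point to MAR would be taken as support for an estimate that could still be biased.

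This is more than a formality in this trial. The sample size section allows for 20% attrition. The arms differ in burden and support: 8 videos and about 5 minutes per exercise set against 3 videos and under 3 minutes, with the Ask Experts feature in the intervention arm only. Dropout related to pain or to lack of benefit, and different between arms, is plausible, though the article neither shows nor excludes it.

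**Working it through.** **1. The plan's own figure.** Inputs from Sample Size and Power Calculations: 60 per arm, 20% attrition, two-sided alpha 0.05, power 90%, detectable difference 0.7 SD.
- Analysed per arm: 60 × 0.8 = 48.
- Detectable difference: (1.960 + 1.282) × √(2/48) = 0.662 SD by the normal approximation, 0.669 SD with the t distribution. Both round to 0.7, so the figure reproduces and serves as the yardstick below.

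**2. Why the step cannot work.** Write the week-12 outcomes as observed and missing parts and let r be the missingness indicator:

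f(y_obs, y_mis, r) = f(y_obs, r) × f(y_mis | y_obs, r)

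The data inform only the first factor. MAR and NMAR are statements about the second: whether those who are missing follow the same distribution, given their observed history, as those who are seen. Any choice for the second factor leaves the fit to the observed data unchanged.

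**3. Illustration by simulation.** All inputs are assumed: 60 per arm, about 20% missing at week 12, true effect −0.70 SD, baseline to week-12 correlation 0.5, 2,000 runs per mechanism. The check tests missingness against baseline pain. The estimate is the baseline-adjusted difference among those observed. In the NMAR case, dropout depends on the part of the week-12 value that baseline does not explain, in opposite directions in the two arms.

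| Mechanism | Check rejects | Mean estimate (true −0.70) |
|---|---|---|
| Missing completely at random | 5% | −0.70 |
| MAR | 97% | −0.70 |
| NMAR | 5% | −1.01 |

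The check raises an alarm where the adjusted estimate is unbiased and is silent where it is biased. It separates MAR from missing completely at random, but not MAR from NMAR.

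**4. Size on the continuous scale.** If a fraction π is missing in one arm and those outcomes are δ SD worse than MAR predicts, the group difference moves by π × δ.
- π = 0.20, δ = 0.5: 0.10 SD; 0.10/0.7 = 14% of the stated difference.
- π = 0.20, δ = 1.0: 0.20 SD; 0.20/0.7 = 29%.
- Other attrition, same two δ: 0.05 and 0.10 SD at 10% missing; 0.15 and 0.30 SD at 30%.
- Opposite shifts in both arms double each figure. At 20% missing and δ = 1.0, an apparent 0.7 SD becomes 0.7 − 2 × 0.20 = 0.30 SD.

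The value of δ is an assumption throughout; the article gives none.

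**5. Size for presence of pain.** With 12 of 60 missing in an arm, setting all of them to pain or all to no pain spans 12/60 = 20 percentage points. If MAR predicts prevalence p among the missing, the move from that prediction is at most 20 × (1 − p) points upward or 20 × p points downward: 10 points either way at p = 50%.

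**The case against.** **The wording can be read more mildly.** The article speaks of whether MAR can be assumed and names no test. Describing dropout patterns in order to justify an assumption is ordinary practice. That is fair as far as it goes, but the next sentence makes the choice of method follow from the results of the step, so the switch stands.

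**A reader might infer that the primary analysis itself is left open until the data are seen.** The article does not support that. The Analysis Plan already names linear and generalized linear mixed models, and if MAR is concluded their estimate need not change. What the step leaves open is which missing-data method is applied with them or in place of them.

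**A reader might also infer that Heckman selection is ruled out because pain is a yes/no or 0–4 item, or because no variable predicting dropout but not pain is named.** Neither inference holds. Selection models exist for binary and ordinal outcomes. The model is formally identified without such a variable, though weakly. Heckman is given only as an example, and an article may leave that detail to a fuller document. The same goes for the absence of a sensitivity analysis: alone it would be no finding.

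**The remark on mixed models is mainly a comparison with listwise deletion.** As such it is sound. What stands is that the claimed protection needs MAR and the text does not say so.

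**The sizes are illustrative.** The 20% is a planning allowance, and the article expects few missed observations. The simulation uses a chosen mechanism and checks baseline only, although pain is also collected at weeks 4 and 8. Those data can make MAR more credible, but they cannot establish it.

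**Conclusion.** The concern holds as a defect in a stated rule, not as an omission. The article makes the missing-data method depend on a determination that observed data cannot deliver, and the week-12 pain endpoint falls under that rule. An analysis plan that followed the text would inherit the problem.

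Whether the final estimate would change depends on what the step concluded. A MAR conclusion could leave the mixed-model result as it is; an NMAR conclusion could replace it or set a rival estimate beside it.

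At 20% missing with the shift confined to one arm, departures of 0.5 to 1.0 SD from MAR are worth 0.10 to 0.20 SD. These sizes rest on assumed shifts and are not predictions for this trial. For presence of pain, it is tempting to read 20 points as the possible bias. That figure is the full best-to-worst range in one arm; the shift from the MAR prediction is smaller, about 10 points at a predicted prevalence of 50%.

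**What to change.** - Delete the step that first classifies the missing data and then selects a method.
- State that the mixed models in the Analysis Plan, fitted by likelihood to all available observations of randomised participants with baseline pain in the model, are the primary analysis under an assumed MAR mechanism, whatever the data show. Dropout patterns can still be described, but should not trigger a change of method.
- Qualify the sentence on the robustness of mixed models by adding that it requires MAR.
- Examine NMAR only in a prespecified sensitivity analysis, for example delta-adjusted multiple imputation that worsens imputed week-12 pain in the intervention arm in steps until the conclusion changes. A selection model may be kept as a further sensitivity analysis, not as a replacement for the primary one.

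The cost is a few sentences of wording and one extra analysis. No new data and no change to the sample size are needed.

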## Results

This trial is currently open for recruitment. The anticipated completion date for the study is July 2017. The primary endpoint for the study is absence or reduction of pain reported by the participants at week 12 post-intervention.

##  Discussion

### Hypothesis

Low cost and pragmatic self-care strategies for symptom management may hold great promise for improving patients’ quality of life [6,19]. To date, limited research has been designed to help breast cancer survivors to manage their daily distressful symptoms, including pain. This clinical trial focuses on primary outcomes of pain reduction and secondary outcomes of relief of symptoms related to lymphedema, limb volume difference by infra-red perometer, BMI, quality of life to refine procedures and estimate effect size for the future efficacy of multi-center RCT. We hypothesize that participants in the intervention group will experience no or less severe pain, aching, soreness, and tenderness and better associated quality of life (related to pain, aching, soreness, and tenderness) in comparison with participants in the control group when compared to participants in the control Arm Precaution group.

### Conclusions

The proposed project will directly benefit all women treated for breast cancer who suffer from or are at risk for pain and symptoms related to lymph fluid accumulation by providing a low-cost, technologically-driven delivery model to universally expand the accessibility of The-Optimal Lymph-Flow. With health care reform under way, using Web- and mobile-based technology to develop low cost and pragmatic patient-centered intervention is the key to lessening the health care cost and advancing the science of symptom management.

## Appendix

Multimedia Appendix 1 CONSORT-EHEALTH checklist V1.6.1.

Multimedia Appendix 2 Full proposal review feedback form.

## Abbreviations

BMI: body mass index
MAR: missing at random
NMAR: not missing at random
PIQ-6: Pain Impact Questionnaire-6
RCT: randomized controlled trial
